## Discussion

The field of pDoC currently faces two fundamental challenges: first, the absence of large-scale, long-term longitudinal follow-up data in Chinese populations—as existing evidence is predominantly derived from European and North American cohorts (16, 17) and therefore inadequately reflects the disease trajectories shaped by China’s distinct etiological profile, healthcare resource distribution, and rehabilitation culture; second, the predominance of prognostic prediction models based on cross-sectional or short-term follow-up data, which are unable to capture the dynamic evolution of consciousness recovery and consequently deprive clinical decision-making of accurate temporal guidance, resulting in considerable uncertainty in the timing of therapeutic interventions (18). To address these challenges, we designed this single-center, prospective, observational cohort study with a 5-year follow-up period, anchored at the Department of Rehabilitation Medicine, Guangdong Sanjiu Brain Hospital—a nationally recognized leading center for pDoC diagnosis and management. The central objective of this protocol is to establish a high-quality, longitudinal database of long-term outcomes in Chinese patients with pDoC, enabling the systematic characterization of dynamic changes in consciousness recovery, quality of life, and functional status, and the construction of precision prognostic prediction models tailored to the domestic population, thereby providing an evidence base for individualized intervention strategies.

This study achieves several important methodological advances. The rigorous prospective longitudinal design, with a 5-year follow-up period substantially exceeding that of most published studies (typically 1–2 years), enables comprehensive characterization of both the critical time windows for consciousness recovery and the features of long-term stable plateaus—directly addressing the predominant reliance on cross-sectional observations in the field and providing unprecedented longitudinal data to elucidate the time-dependent nature of recovery. In terms of data integration, this protocol transcends the limitations of traditional single-source clinical data by harmonizing structured electronic medical records, standardized neuropsychological assessments (CRS-R), objective neuroimaging (structural and functional MRI), serum biomarkers of neural injury, and patient-reported outcomes (health-related quality of life instruments). Notably, the application of internationally standardized instruments with blinded assessment for the definition of core outcome variables substantially reduces misclassification and information bias. This multisource data integration is anticipated to reveal deep associations between clinical phenotypes and biological mechanisms, uncovering interaction patterns that conventional single-modality research cannot identify. To mitigate the most critical methodological threats in DoC research—attrition bias and measurement bias—we have implemented distinctive safeguards: a hybrid follow-up strategy combining telephone interviews and outpatient visits, with a quality target of ≥ 85% follow-up completion rate; uniform training and certification of all assessors; blinded adjudication of all primary outcome events by an independent Endpoint Adjudication Committee; and independent dual-reader review of all neuroimaging data. As a single-center study, we are able to achieve a highly standardized operational workflow and quality control system, with all data collection adhering to unified standard operating procedures (SOPs). The study has been prospectively registered on an international clinical trial registry and will be reported in compliance with the STROBE statement; the level of quality control substantially exceeds the average for comparable observational studies.

The choice of a prospective cohort design was deliberate and methodologically grounded. Prospective cohort design is the recognized standard for pDoC natural history and prognostic investigation, as reflected by all landmark studies cited in this protocol (13–17). More fundamentally, the Fine-Gray competing-risk model—a core analytical feature of this protocol—requires prospectively ascertained event-time data and is methodologically incompatible with a retrospective case–control framework. The prospective design additionally enables modeling of time-dependent covariates (notably, treatment intensity) to distinguish natural recovery trajectories from treatment-mediated change, and uniquely permits characterization of the temporal dynamics of recovery—information that is inaccessible to case–control designs. Nevertheless, to address the analytical goal of comparing patients who recover with those who do not, a pre-specified nested comparison between recovery-positive and recovery-negative groups will be conducted within the cohort framework using the Fine-Gray model with pre-specified clinical prognostic predictors.

The 5-year follow-up horizon was selected to align with the most comprehensive existing prospective pDoC cohorts (13, 15) reporting 5-year cumulative recovery rates of 42.3–48.7% in Chinese populations, and to capture late recovery events beyond the conventional 12-month observation window that dominates prior literature.

Despite these methodological strengths, several limitations warrant acknowledgment. As a single-center study, this protocol may face limitations in sample representativeness, and caution will be required when generalizing findings to other regions of China. Additionally, extended follow-up duration may increase attrition rates, and certain self-reported variables may be susceptible to recall bias. Detailed contingency measures have been developed to address these risks: an additional 20% recruitment buffer has been incorporated into the sample size calculation to accommodate anticipated dropout; multiple imputation by chained equations will be employed to handle missing data, and robustness will be evaluated using pattern mixture models and tipping point analyses; baseline characteristics will be compared between participants lost to follow-up and completers, with inverse probability weighting applied to correct for potential selection bias; objective medical records will be prioritized over self-reported data wherever feasible; and sensitivity analyses will be performed to validate the reliability of primary conclusions. The limitations of the single-center design will be explicitly acknowledged in the discussion, and future multicenter validation research will be recommended.

Upon successful completion of this protocol, the resulting data will provide critically needed, locally contextualized evidence to support pDoC diagnosis and management in Guangdong and the broader South China region. The study will supply high-quality parameters for consciousness recovery prediction models and promote a paradigm shift from empirical intervention toward precision timing of therapeutic strategies. As a leading single-center pDoC cohort in China, the standardized data collection workflow and quality control system established by this study will serve as a reference template for similar investigations at other institutions, facilitating the methodological standardization of pDoC research in China. Most importantly, the prognostic prediction tools developed from this study will provide individualized decision support for clinicians, assist patient families in planning rehabilitation pathways and resource allocation, and ultimately improve patient quality of life while reducing the societal burden of caregiving. This protocol establishes a methodological benchmark for high-quality single-center cohort research in the pDoC field and lays a robust data foundation and technical infrastructure for future multicenter collaborative investigations.

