### Bias control

To minimize selection bias, a systematic three-step recruitment procedure (screening, informed consent, and baseline assessment) will be implemented with independent review by a multidisciplinary team. To address follow-up bias, a hybrid surveillance strategy combining telephone interviews and outpatient visits will be employed, with a target follow-up completion rate of ≥ 85% and active tracing of participants lost to follow-up. Confounding bias will be controlled through multivariable regression models incorporating documented potential confounders, with effect modification explored in prespecified subgroup analyses. To mitigate performance and detection bias, outcome assessors will be blinded to baseline results; all primary outcome events will be adjudicated by an independent Endpoint Adjudication Committee in a blinded manner; and all neuroimaging data will be independently reviewed by two radiologists. The study has been prospectively registered on an international clinical trial registry and will be reported in accordance with the STROBE statement.

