### Sample size calculation

The sample size was determined based on 5-year consciousness recovery rates reported in the existing literature on prolonged disorders of consciousness. Chen et al. (13) reported a 5-year consciousness recovery rate of 42.3% in a prospective cohort of Chinese patients; a systematic review by Giacino et al. (14) indicated recovery rates of approximately 35–50% among patients with pDoC following TBI; and a recent longitudinal study by Yan et al. (15) reported a 5-year cumulative recovery rate of 48.7%. Given that the present study enrolls a mixed-etiology cohort (traumatic and non-traumatic) and employs a competing-risk analytical framework, a conservative 5-year cumulative incidence rate of 34% (annual event rate: 8%) was adopted as the basis for sample size estimation, ensuring adequate statistical power. Assuming a hazard ratio (HR) of 1.3, two-sided *α* = 0.05, 80% statistical power, and an exposure proportion of 30%, the required number of events was calculated as 544 using the Schoenfeld formula. Adjusting for an anticipated 15% loss to follow-up over the 5-year period, the target sample size was determined to be 1,000 participants. This sample size will ensure adequate statistical power for the primary survival outcome, support detection of secondary outcomes (functional recovery and quality-of-life changes), enable the identification of moderate effect sizes (Cohen’s *d* ≥ 0.5 or OR ≥ 1.5), and accommodate prespecified subgroup analyses. Prespecified subgroup analyses will evaluate the influence of age, sex, and baseline severity; assuming a subgroup prevalence of 30% and an event rate consistent with the overall cohort, ≥ 80% power will be achievable for detecting HR ≥ 1.5 within each subgroup.

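### The Discussion claims a 20% recruitment buffer that the sample size calculation does not contain; under the stated inputs, 1,000 participants include no dropout reserve of any size

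*Protocol article*

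**What the plan says.** Two sections of the protocol article describe how dropout entered the sample size.

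- Discussion, limitations paragraph: "an additional 20% recruitment buffer has been incorporated into the sample size calculation to accommodate anticipated dropout". It comes first in the list of contingency measures that answers the authors' concern about attrition and recall bias.
- Sample size calculation: "Adjusting for an anticipated 15% loss to follow-up over the 5-year period, the target sample size was determined to be 1,000 participants". The inputs there are "Assuming a hazard ratio (HR) of 1.3", "two-sided *α* = 0.05", 80% power and 30% exposed. From these, "the required number of events was calculated as 544 using the Schoenfeld formula". For the event probability, "a conservative 5-year cumulative incidence rate of 34% (annual event rate: 8%) was adopted as the basis for sample size estimation".

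The Bias control section plans follow-up "with a target follow-up completion rate of ≥ 85% and active tracing of participants lost to follow-up". That target matches a 15% loss.

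**The concern.** Both sections describe the same calculation and give different attrition figures, 15% and 20%. No 20% term appears where the calculation is set out. This is a conflict between two statements in the article, so it is not a detail left to a fuller document.

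The Discussion presents the buffer as already built in. A reader could take it that substantial dropout leaves the planned 80% power intact, and could plan recruitment and retention on that basis. The check is whether 1,000 contains a dropout allowance of either size.

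**Working it through.** **Inputs**, all from Sample size calculation unless noted: HR 1.3; two-sided alpha 0.05; power 80%; exposed proportion 0.30; 544 events; 34% five-year cumulative incidence (8% per year); 15% loss; N = 1,000. From the Discussion: 20% buffer.

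**1. Reproduce the plan's own figures.**
- Events (Schoenfeld): (1.960 + 0.842)² / [0.30 × 0.70 × (ln 1.3)²] = 543. The stated 544 reproduces.
- Incidence: 1 − 0.92⁵ = 0.341. The stated 34% reproduces.

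**2. Go from events to participants.** Participants before dropout = events / incidence = 544 / 0.34 = 1,600.

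**3. Add dropout**, reading each percentage as a loss (divide by 1 − d) and as an inflation (multiply by 1 + d).
- 15%: 1,600/0.85 ≈ 1,882; 1,600 × 1.15 = 1,840.
- 20%: 1,600/0.80 = 2,000; 1,600 × 1.20 = 1,920.
- 20% on top of 15%: (1,600/0.85) × 1.20 ≈ 2,259; 1,600/(0.85 × 0.80) ≈ 2,353.

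None gives 1,000, and 1,000 is already below the 1,600 needed with no dropout.

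**4. Try readings that might rescue 1,000.**
- Inflating the event count itself: 544/0.85 = 640; 544/0.80 = 680; 544/(0.85 × 0.80) = 800.
- Using the cited five-year rate of 48.7%: 544/0.487 ≈ 1,117 before dropout; 1,315 with 15% loss; 1,397 with 20%.
- Using 50%, the top of the cited range: 544/0.50 = 1,088 before dropout.
- Working backwards: 1,000 enrolled would give 544 events only at an incidence of 544/850 = 64% (15% loss) or 544/800 = 68% (20% loss). Neither figure is in the document.

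**5. Power at N = 1,000 and 34% incidence.** Power = Φ(√(D × 0.21) × ln 1.3 − 1.96), where D is the number of events and those lost are counted as contributing none.
- No loss: D = 340, power 60%.
- 15% loss: D = 850 × 0.34 = 289, power 53.3%.
- 20% inflation: D = (1,000/1.20) × 0.34 ≈ 283, power 52.5%.
- 20% loss: D = 800 × 0.34 = 272, power 50.9%.

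**6. Split the shortfall.** About 20 of the points lost from 80% arise before any dropout (80% to 60%). A 15% loss takes about 7 more. Replacing 15% by 20% takes 0.8 points (inflation reading) to 2.4 points (loss reading).

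**The case against.** The strongest reply is that the two percentages are different quantities and lie close together. A recruitment buffer is most naturally an inflation of the base number, whereas the calculation gives a loss fraction. A 20% inflation absorbs 1 − 1/1.20 = 16.7% loss, and a 15% loss needs 1/0.85 − 1 = 17.6% inflation. At N = 1,000 the two imply 833 and 850 evaluable participants, a difference of 17. This stands: the numerical conflict is small, and the sentence need not promise protection against a 20% loss. It does not rescue the claim that the buffer was incorporated, because neither reading leads to 1,000.

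It is also fair to say that the low power belongs to the step from events to participants and not to the Discussion sentence. A reader might infer that the 15% versus 20% mismatch costs nearly 30 points of power; step 6 shows that it does not.

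A reader might also infer that the study has no protection against attrition. The document does not support that. It plans hybrid follow-up with active tracing, comparison of those lost with completers, inverse probability weighting, multiple imputation, pattern mixture models and tipping point analyses. These address retention and bias. None adds back the recovery events that an undersized cohort lacks.

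Finally, counting those lost as contributing no events is a worst case. The Loss to follow-up section censors them at last valid contact, so earlier recoveries still count.

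**Conclusion.** The point holds for the recruitment buffer only. The Discussion attributes to the sample size calculation a 20% allowance that is not there, and the calculation's own inputs leave 1,000 with no dropout reserve of any size. It would be equally wrong to infer that a 15% reserve exists and only the extra 5% is missing: 1,000 is 600 short of the number needed before dropout.

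At N = 1,000, power for HR 1.3 is about 60% with no loss, 53% with 15% loss and 51% with 20% loss, against the planned 80%. These figures assume 34% incidence, 30% exposed, two-sided 0.05 and the Schoenfeld approximation. Given those assumptions, the two loss figures are lower bounds and 60% is the ceiling. The attrition discrepancy itself accounts for about 1 to 2.5 points; the main shortfall comes from the move from 544 events to 1,000 participants.

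**What to change.** - Delete the 20% buffer claim from the limitations paragraph of the Discussion.
- Use one attrition figure in Sample size calculation and Discussion, and say whether it is a loss fraction or an inflation factor.
- State that, under the stated inputs, 1,000 includes no reserve for dropout. Changing 20% to 15% in the Discussion would remove the contradiction but still imply a reserve that is not there.
- Replace the 80% power claim with the power at N = 1,000 and 34% incidence for HR 1.3: about 60% with no loss (340 events), 53% with 15% loss (289) and 51% with 20% loss (272). Note that the loss figures are lower bounds.

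The cost is wording and a short power statement; no data collection or analysis changes. The stated power becomes less favourable. If the sponsor wants to keep 80% power for HR 1.3, the step from events to participants has to be reworked, which is a design decision and not an edit.
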